#### Families

Eligible families are all families with small children aged 0 to 3 years undergoing treatment by the participating pediatricians. The pediatricians ask the families for participation during the preventive medical check-ups of the U3 up to the U7a (medical check-ups with the target age of the children) and obtain their informed consent. Language skills in German, Arabic, Italian or Turkish are required for participation. Families, who answer all three surveys receive a 30€ voucher after the last measurement time-point. In addition, families who participate in the interview study section receive an expense allowance of 30€.

### Procedure

#### Summative evaluation

##### Questionnaire survey

Participating families are asked to complete online-surveys including questions concerning sociodemographic information, psychosocial burden, the use of supportive services, as well as questions about information provision and motivation by the pediatrician. In addition, families are either asked to rate their satisfaction with a specific offer, or to state the reasons why they did not use it (see Table S1, Additional file 1, for the operationalization of psychosocial burden and Additional file 2 for the family questionnaire about supportive services). The survey takes place at three measurement time-points: up to 7 days after the medical check-up (t1), 6 weeks after the medical check-up (t2) and again at 6 months after the medical check-up (t3). The same person should answer all three surveys. At each time-point, participating families receive a link to the online-survey via e-mail. The link is valid for 7 days. The online-survey is available in four languages, namely German, Arabic, Italian and Turkish.

Immediately after a participating family leaves the medical check-up, the pediatrician rates in a short paper-pencil questionnaire whether the family is psychosocially stressed, and if so, the degree of psychosocial burden (Questionnaire for pediatricians, Additional file 3). Moreover, the pediatricians are asked whether they have addressed the perceived psychosocial burden with the family and to rate the family’s need for supportive services. At the end of the recruitment of families, the pediatricians answer a second paper-pencil questionnaire about possible confounding variables, such as the structural characteristics of the doctor’s office and work experience (Descriptive questionnaire for pediatricians, Additional file 4).

#### Process evaluation

##### Interviews

As there are different stakeholders involved in the intervention process, we examine the acceptance of the PATH-intervention in the perspective of the pediatricians, families and ECI network members. Trained interviewers will conduct telephone interviews with participants of all three groups who agreed to this optional study section. We select families for the interviews who are treated by an IG-pediatrician and report psychosocial burden according to the first completed online-survey. To obtain a range of variation in the sample of the families, we employ further selection criteria related to the age and gender of the child. All IG-pediatricians who additionally declared their interest for the interview study section are asked to participate in the telephone interview. The ECI network members will be exclusively recruited for the purpose of the interviews.

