##### Observation

For the purpose of the video-assisted observations, we will select a group of participating families by the following criteria: the families are treated by IG-pediatricians, the families report psychosocial burden according to the first completed online-survey, the previous preventive medical check-up was the U3, U4 or U5, and the families agreed to this optional study section. In such cases, the observation of the attending IG-pediatrician takes place during the next preventive medical check-up with the family, the U4, U5 or U6. Afterwards, the researcher on site conducts a short interview with the family. We intend to conduct two observations per participating IG-pediatrician.

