The second secondary distal outcome is the acceptance of the PATH-intervention in the perspectives of all stakeholders involved in the intervention process. With qualitative telephone interviews, we intend to gain a deeper insight into the perspectives of the trained pediatricians, burdened families and ECI network members. This includes their appraisal of the PATH-intervention as well as perceived facilitating and hindering factors. Semi-structured interview guidelines will be developed individually for all three groups. The interviews will start with a narrative entry followed by specific questions targeting the themes of interest. Themes of the interview guidelines are the collaboration between professionals, the perceived individual benefit of the intervention, the procedure of identification and discussion of psychosocial burden, the paths to the ECI and supportive services, as well as potential barriers for tailored referrals to adequate services. Interview guidelines for ECI network members will focus on interprofessional cooperation and referral of families into the ECI system and they will deliver background information about the specifics of the regional ECI networks. The telephone interviews will last approximately 1 h, will be audio-recorded, and transcribed verbatim.

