### Sample size considerations

#### Summative evaluation

In total, we intend to include *N* = 40 pediatricians in the study. In purpose of the planned statistical twins (matched pair approach), each group (IG, CG) should comprise *n* = 20 pediatricians.

Concerning the family sample, we calculated the sample size for the planned analyses (logistic regressions) of the primary outcome (proportion of burdened families making use of supportive services) using the software GPower. The underlying assumptions were a statistical power of 0.80 and a significance level of 5%. Concerning the effect size, we assumed that 50% of the families with psychosocial burden under treatment of IG-pediatricians would use supportive services, compared to only 10% of the burdened families of CG-pediatricians. Furthermore, we assumed that the portion of families with psychosocial burden will be about 15% in the overall sample. About 50% of the eligible families are presumed to participate in the online-survey, from which about 30% will drop out of the study up to the last follow-up measurement time-point. Thus, to detect a significant effect concerning the use of supportive services by families with psychosocial burden contrasting intervention to control group, a total of *N* = 800 families should be asked to participate by the pediatricians, namely *n* = 20 families per each pediatrician.

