#### Process evaluation

We intend to interview *N* = 10 pediatricians of the IG and N = 10 ECI network members. Of the participating families, *N* = 20 families under treatment of IG-pediatricians should be interviewed. For these cases, we use purposeful sampling aiming at maximum variability regarding age and gender of the child, as well as concerning the reported psychosocial burdens in the first online-survey.

A similar purposeful sampling is used to select the sample for the observation study section. The observations are conducted with *N* = 14 families of IG-pediatricians. The families are selected based on the following criteria: the family, which is under treatment of the IG-pediatrician, attended the U3, U4 or U5 at the time of recruitment. In addition, the family reports considerable psychosocial burden in the first online-survey.

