Table 1 displays a summary of the outcomes, measurements, data source and measurement time-points, as well as methods of analysis.

**Table 1 Tab1:** Summary of outcomes, measurements, data source and measurement time-points, and methods of analysis

Outcomes	Measurement	Data source	Measurement time-point			Data analysis
			t1	t1	t2	
Use of supportive services by families with psychosocial burden (primary outcome)	Online-survey	Families	x	x	x	Comparison of intervention & control group using generalized linear mixed models
Correctly identified families with psychosocial burden (secondary outcome, proximal)	Paper-pencil-questionnaire	Pediatricians	x			
Information provision & motivation of families with psychosocial burden by the pediatrician (secondary outcome, proximal)	Online-survey	Families	x	x	x	
Cost-effectiveness ration of the PATH-intervention (secondary outcome, distal)	Direct costs of the intervention, health insurance claim data	Association of Statutory Health Insurance Physicians Baden-Wuerttemberg, Statutory Health Insurance “AOK” Baden-Württemberg	Throughout the study.			Calculation of incremental cost-effectiveness ratios (ICERs)
Acceptance of the PATH-intervention (secondary outcome, distal)	Telephone interviews	Families with psychosocial burden, IG-pediatricians, ECI network members	Throughout the online-survey data collection phase.			Qualitative content structuring
Treatment fidelity	Video-assisted observations	IG-Pediatricians	The next preventive medical check-up (U4-U6) of a participating family with psychosocial burden.			Qualitative analysis (incl. Conversation analysis)

Note: t1/ t2/ t3 = first/ second/ third measurement time-point; “U” = U-Untersuchung (preventive medical check-up for children aged 0-3 years)

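### Family interviews about routes to ECI services are confined to burdened intervention-group families and may fall before their t2 or t3 report of service use, which can bias the primary outcome in favor of the intervention

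*Protocol article*

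**What the plan says.** **Who is interviewed.** Under Procedure, Process evaluation, Interviews: "We select families for the interviews who are treated by an IG-pediatrician and report psychosocial burden according to the first completed online-survey". Sample size considerations, Process evaluation, sets a target of 20, again confined to one arm ("families under treatment of IG-pediatricians should be interviewed"). Participation is optional. No CG counterpart is described.

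**What is discussed.** Secondary outcomes gives a length of about one hour and lists among the themes "the paths to the ECI and supportive services, as well as potential barriers for tailored referrals to adequate services".

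**When.** Table 1, in the row on acceptance, gives "Throughout the online-survey data collection phase". This is a window for the whole study. No section ties a family's interview to its own t2 or t3.

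**Filming.** Fourteen IG families who are burdened at t1 are to be filmed: "the observation of the attending IG-pediatrician takes place during the next preventive medical check-up with the family". Treatment fidelity adds a short talk afterwards on whether the doctor behaved differently from usual.

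**What it may affect.** The primary outcome is use of at least one of 14 listed services by burdened families during the study period, reported in the surveys at t1, t2 and t3. Use is asked only for services that the family says it knows.

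**How it is handled.** The main model and the three sensitivity analyses under Data analysis do not separate these contacts from PATH. The limitations in the Discussion mention the IG observations, but only as sensitizing pediatricians. The family interviews do not appear there.

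**The concern.** The primary comparison should differ between arms only in whether the pediatrician works under PATH, apart from confounding that the matching and the propensity score are meant to handle. Here a second difference is built in by the research itself. An hour spent with a researcher on how families reach ECI services, and on what stops them, concerns the same behavior that the primary outcome measures. If it takes place before the family's t2 or t3 survey, it can make services better known or prompt a family to use one, and that use is credited to PATH. Because use is asked only for known services, greater awareness also opens more of the use questions. The information and recommendation outcomes are asked behind the same filter.

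The plausible direction is toward the hypothesis. The families concerned could be a large part of a small arm, and the exposure cannot be undone in the analysis once it has happened.

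**Working it through.** **1. Reproduce the plan's sample size.** Inputs from Sample size considerations: service use of 10% in CG and 50% in IG ("we assumed that 50% of the families with psychosocial burden under treatment of IG-pediatricians would use supportive services"); power 0.80, alpha 5% (two-sided assumed, since sidedness is not stated), 15% burdened, 50% participation, 30% dropout.

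Pooled two-proportion formula, mean proportion 0.30:

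n per arm = [1.960 × √(2 × 0.30 × 0.70) + 0.842 × √(0.25 + 0.09)]² / 0.40² = 19.4, so 20 per arm and 40 in total.

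40 / (0.15 × 0.50 × 0.70) = 762 families asked, or 19.05 for each of 40 pediatricians. Rounded up, 20 × 40 = 800, which is the plan's figure.

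**2. Burdened IG families expected.**
- At t1: 400 asked × 0.50 × 0.15 = 30.
- At t3: 30 × 0.70 = 21.

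**3. Share contacted if the targets are met.**

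| Assumed share burdened | Burdened IG families at t1 | Interviewed (20) | Filmed (14) |
|---|---|---|---|
| 12.9% (Background) | 25.8 | 78% | 54% |
| 13.8% (Background) | 27.6 | 72% | 51% |
| 15% (planning value) | 30 | 67% | 47% |
| 20% (assumption) | 40 | 50% | 35% |

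The last row is not far-fetched. The study counts a family as burdened from three risk factors, whereas the 12.9% in the Background refers to four or more.

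**4. Timing.** Families are chosen on the t1 survey, so an interview always follows t1. Table 1 then allows it at any point while surveys are being collected. An early recruit could be interviewed after its own t3. A late recruit interviewed within that window would be seen before or around its own t3. The text neither requires nor excludes either order. With only 21 burdened IG completers expected, taking all 20 interviews from families that have returned t3 would need 20/21 = 95% of them to agree.

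**5. Illustration only.** Nothing in the documents gives the effect of an interview. Assume no PATH effect, 10% use in both arms, 67% of IG interviewed, all before the decisive survey, and q added to the probability of use in those interviewed. Then IG use = 0.10 + 0.667 × q. The last column is the chance of a significant result favoring IG with 21 per arm (normal approximation, no clustering), against a nominal 2.5%.

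| q | IG use | CG use | Chance of a significant result favoring IG |
|---|---|---|---|
| 5 points | 13% | 10% | 5% |
| 10 points | 17% | 10% | 9% |
| 20 points | 23% | 10% | 21% |
| 30 points | 30% | 10% | 36% |

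To produce the whole planned difference of 40 points by itself, the interview would need q = 0.40 / 0.667 = 60 points.

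**The case against.** A good deal can be said for the plan.

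- **Timing is open, not wrong.** A reader might infer that most burdened IG families are interviewed during their follow-up. Table 1 does not say so: it gives a study-level window, and an article may leave scheduling per family to the full protocol. This stands against any claim that the interviews will precede t3. It does not remove the point, because the window that is stated allows it.
- **The shares are targets.** Interviews are optional, and two thirds depends on 15% burdened. This stands.
- **Both arms already see the list of services.** Every family is asked about the 14 services in the surveys, and for a given service rates it or gives reasons for not using it. Only the increment of the interview matters, and no offer or referral is described as part of it. This stands and makes a large effect less likely. It does not cancel the difference, because the surveys are common to both arms and the interview is not.
- **Filming is weaker still.** A reader might treat the filmed check-up as a second contact of the same kind. The check-up is the family's next routine one, the researcher is not in the room, and the talk afterwards is described only as asking about the doctor's behavior. No check-up ages are given, so filming cannot be placed before t3. The effect on pediatricians is already disclosed. This stands.
- **Acceptance of PATH can be asked only of those who had it.** True, but this explains whom to interview, not when.

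**Conclusion.** The point holds as a risk that the stated design leaves open. A contact confined to the IG half of the primary analysis population, on the subject of the primary outcome, may fall before that outcome is reported, and nothing in the analysis separates it from PATH. On planning figures it would reach about two thirds of burdened IG families (20/30), or half or less if 20% or more are burdened. This rests on the targets being met and on at least some interviews preceding t2 or t3.

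A reader might go further and conclude that the primary outcome is biased, or biased by some stated amount. The documents do not support that. They contain no evidence on what an interview does, and the illustration shows only how the result would respond to assumed effects. Nor could a contact effect of the sizes illustrated account for a difference as large as the planned 50% against 10%. The supportable statement is that the interviews can bias the comparison in favor of IG, by an unknown amount, and that this is avoidable.

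**What to change.** **Interviews.** State in the Interviews section that a family's telephone interview takes place only after its t3 survey has been returned or its t3 link has expired (links are valid for 7 days), and change the timing in the acceptance row of Table 1 accordingly. The rule must be in force before interviews begin.

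**Filmed check-ups.** Keep the design, since it depends on the next check-up. Record for each filmed family whether filming came before its t3 survey. Extend the limitation in the Discussion from pediatricians to IG-only contact with families.

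**What not to do.** Counting, for contacted families, only the use reported before the contact would shorten follow-up in IG while CG keeps its six months. Use is reported only at t1, t2 and t3, so a family interviewed before t2 would contribute t1 alone. Such an analysis should not be used unless CG follow-up is cut comparably. Excluding interviewed families is no better: about 30 − 20 = 10 burdened IG families would remain at t1.

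**Cost.** Wording in one section and one table row. Interviews move to about six months after the check-up, with poorer recall of how burden was raised and discussed. About 9 of the 30 families will have dropped out by then and will be harder to reach, so the target of 20 may be harder to meet. Fieldwork lasts somewhat longer.

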##### Observation

For the purpose of the video-assisted observations, we will select a group of participating families by the following criteria: the families are treated by IG-pediatricians, the families report psychosocial burden according to the first completed online-survey, the previous preventive medical check-up was the U3, U4 or U5, and the families agreed to this optional study section. In such cases, the observation of the attending IG-pediatrician takes place during the next preventive medical check-up with the family, the U4, U5 or U6. Afterwards, the researcher on site conducts a short interview with the family. We intend to conduct two observations per participating IG-pediatrician.

### Study measurements and outcomes

Central for answering the research questions is to assess the risk factors and perceived psychosocial burden of the families. We therefore apply an additive index and count up the risk factors asked for, as is commonly used in research and previous studies [1, 20, 21]. The index comprises six domains, namely the (a) family background, (b) parent’s individual preconditions for dealing with care challenges, (c) parent’s psychological health, (d) difficulties during pregnancy and in interaction with the child, (e) special care challenges regarding the child, and (f) problematical caring behavior. Each domain consists of a set of questions asking for specific risk factors such as low educational qualifications, overcrowding, conflicting partnership, depression, early pregnancy or parental strains. In this context, we utilize commonly used instruments, e.g. the Patient Health Questionnaire (PHQ-4 [22, 23]) measuring parents’ depressive symptoms and the German Version of the Parenting Stress Index assessing challenges and the burden of being a parent [24]. In addition, we apply questions previously used in the representative study concerning the psychosocial burden of families with small children in Germany [25]. Table S1 (Additional file 1) shows the domains and assessed risk factors, and their operationalization with references to the applied, published instruments in detail. In the form of a patient-reported outcome, the participating families themselves answer the questions that underlie the assessment of these risk factors in the online-survey. In line with previous studies, which used the same risk factors as indicators for psychosocial burden [20], families meeting three or more risk factors are judged to have considerable psychosocial burdens (for the calculation of the additive index indicating psychosocial burden, please see Additional file 1).

#### Primary outcome

The primary outcome is the use of supportive services by families with psychosocial burden in the course of the study period. The family survey therefore contains a list of 14 predefined supportive ECI services (Table S2, Additional file 5). For each of these services, the families are asked whether they know about it. If this is the case, they are asked whether they have made use of the service or not (yes-no question). These questions were specifically developed for this study (Family questionnaire about supportive services, Additional file 2). Usage is given when burdened families made use of at least one of the 14 supportive services.

#### Secondary outcomes

Secondary outcomes are classified as proximal and distal outcomes. Proximal secondary outcomes are conceptualized as directly affected by the intervention and observable close to the intervention. In contrast, distal secondary outcomes are located more distant to the intervention and are likely influenced by other external factors than the intervention.

One secondary proximal outcome is the proportion of correctly identified families with psychosocial burden by the pediatricians. With one question, the pediatricians are directly asked whether they judge the family as burdened or not (yes-no question; Questionnaire for pediatricians, Additional file 3). Another two secondary proximal outcomes are, on the one hand, the information provision and, on the other, the motivation of the family with psychosocial burden by the pediatrician. To find this out, the list of the predefined supportive services in the family survey includes questions regarding these two aspects (Family questionnaire about supportive services, Additional file 2). Families, who have already stated to know about a specific supportive service, answer whether the pediatrician informed them about it and recommended them to use it.

One secondary distal outcome is the ratio between costs of the intervention and its effectiveness. In a first step, the total costs of the PATH-intervention will be calculated from the healthcare perspective. The following three aspects form part of the costs of the PATH-intervention: (1) the mandatory one-day-training program for the pediatricians, (2) the continuous participation in the IQCs (twice a year), and (3) reimbursement of certain aspects of the PATH intervention (e.g. identification of burdened families, information provision). All of the three aspects are associated with direct costs, which will be collected from the Association of Statutory Health Insurance Physicians of the German state of Baden-Wuerttemberg and outlined from the healthcare perspective. Both the one-day training program and the participation in IQCs are additionally associated with training credit points for the participating pediatricians, which will be monetarized using opportunity costs and outlined as an additional (societal) perspective. As part of a budget-impact analysis, health insurance claim data from the Statutory Health Insurance “AOK” Baden-Württemberg will be inspected in order to identify the number of individuals that might be applicable to the PATH-intervention in the case of a broader rollout of the program.

The second secondary distal outcome is the acceptance of the PATH-intervention in the perspectives of all stakeholders involved in the intervention process. With qualitative telephone interviews, we intend to gain a deeper insight into the perspectives of the trained pediatricians, burdened families and ECI network members. This includes their appraisal of the PATH-intervention as well as perceived facilitating and hindering factors. Semi-structured interview guidelines will be developed individually for all three groups. The interviews will start with a narrative entry followed by specific questions targeting the themes of interest. Themes of the interview guidelines are the collaboration between professionals, the perceived individual benefit of the intervention, the procedure of identification and discussion of psychosocial burden, the paths to the ECI and supportive services, as well as potential barriers for tailored referrals to adequate services. Interview guidelines for ECI network members will focus on interprofessional cooperation and referral of families into the ECI system and they will deliver background information about the specifics of the regional ECI networks. The telephone interviews will last approximately 1 h, will be audio-recorded, and transcribed verbatim.

